### Patients and settings

Patients are recruited from the Section for Sports Traumatology, Department of Orthopedic Surgery, Bispebjerg-Frederiksberg Hospital and from The Shoulder-Elbow Unit, Herlev-Gentofte Hospital, both in Denmark. Additional inclusion sites may be added.

Patients may be enrolled in the study provided they meet all of the inclusion criteria:Age minimum 18 yearsA clinical diagnosis of traumatic full-thickness rotator cuff (RC) tear involving the supraspinatus tendon (full thickness and width) verified by arthroscopyA repairable tear

In trauma the trauma mechanism should be described. Typically it will be a forced abduction and external rotation to mitigate for a fall, a fall on the outstretched arm, a pull in the arm or a shoulder luxation. No previous symptoms are implied within the definition of a traumatic tear.

Patients are excluded if they fulfill any of the following exclusion criteria:A non-traumatic RC tear of the shoulderAn isolated teres minor or subscapularis tearA partial-thickness/partial-width tearPrior shoulder surgery (all shoulder joints)A clinical diagnosis of glenohumeral osteoarthritis (OA), rheumatoid arthritis or periarthrosisUnable to speak or read DanishUnable to perform and maintain the exercise therapyOther conditions that negatively influence compliance, or place the patient at increased risk, or otherwise make them unsuitable for participation

Orthopedic surgeons perform an initial screening of all patients referred to the department for surgery. If the patients fulfill the eligibility criteria they are referred to the principal investigator, who performs the final eligibility assessment, give the patient detailed information about the study and ask for consent to participate in the study. If the patient consents to participate a baseline assessment visit is performed between 1 and 14 days before surgery, on the understanding that the patient is not finally included and allocated until the surgeon verifies a total and repairable supraspinatus tear. After surgery the orthopedic surgeon provides surgery information (verifying reparable tendon (s)), and included patients are electronically randomized (described in “Allocation, randomization and sequence generation”).

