The Patient Global Rating Scale (GRS) is used to obtain a global/general impression of recovery from baseline to 6, 12 and 52 weeks postoperatively with the question: “Compared to when this treatment first started (before surgery), how would you describe your shoulder this last week?” This is assessed on a 15-point scale where − 7 represents vastly worse, 0 represents unchanged, and + 7 represents much better [57–59].

Patients are also asked about perceived pain using a NPRS [60, 61] with three questions: “On a scale from 0-10, where 0 equals no pain and 10 the worst imaginable pain, how much pain do you feel in your shoulder during resting? / How much pain do you feel in your shoulder during activity? / What is the maximal shoulder pain you have experienced within the past 24 hours?”

Further, patients are asked to report use of analgesics (type (paracetamol or opioids)/amount). Secondary clinical outcomes consist of active and passive shoulder elevation ROM in the scapular plane (standing); external and internal shoulder rotation (in 90° abduction when supine) [62, 63], as measured by digital inclinometer (Baseline Evaluation Instruments, model 12–1057 from Procare). Maximum voluntary isometric contraction (MVC) of shoulder external and internal rotation (sitting) and elevation in the scapular plane [62, 64, 65] is measured by dynamometer (IsoForceControl, model EVO2, 10-400 N, Medical Device Solutions AG). Furthermore, intraoperative information (including details of tendon repair) and patient-reported number of sick-leave days from work/time until return to work and leisure activities are registered.

Tendon healing characteristics of the repaired supraspinatus tendon (SST) and the subacromial space (SAS) are investigated at 12 months follow-up using US greyscale. The SAS and the SST thickness are also potentially important factors in understanding the pathogenesis of rotator cuff pathology [66, 67], tendinopathy [68] and ruptures [69] a year after repair [70]. Furthermore, power Doppler (PD) US is used for measuring vascularization as a sign of pathology and healing [70, 71]. The US examination is performed by the principal investigator ([name]) using a Hitachi Ascendus scanner and Hitachi Medical Systems Linear standard probe type L75 18–5 MHz 50-mm transducer (Hitachi Aloka Medical) and the musculoskeletal program. The depth preset is 2.50 cm and focus is adjusted, so it is placed right under the tendon.

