### Allocation, randomization and sequence generation

After baseline tests and surgery the patients will be randomized equally (1:1) to receive either the PR protocol or the UC protocol. The computer-generated randomization to one of two treatment arms is performed based upon permuted random blocks of variable size (4–8 in each block) using the Procordo Research Platform. To counter potential imbalance in the randomization, stratification by trial site and age (+/− 57 years) will be employed together with blocking. The randomization is performed by a person (SW) with no clinical involvement in the trial, and the person notifies the patient and clinical study staff of the treatment allocation. The allocation will be concealed in a password-protected Research Platform only accessible by the senior researcher and the independent data manager (Procordo).

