The primary analysis at week 12 will be by analysis of covariance (ANCOVA) on change from baseline in the WORC domains as dependent variables, with group allocation (two levels) and time (week 6 and 12), gender and site as fixed factors, whereas age and baseline values will be analyzed as covariates. Secondary outcome measures will be analyzed by multiple logistic regression for binary outcome measures (re-tear, tendon healing, recurrence of symptoms (e.g. pain and function), complications) and by ANCOVA for the continuous outcome measures (pain, patient-reported outcomes, surgery information, strength, ROM) as dependent variables (individually), with group allocation and time as fixed factors, and site and baseline values as covariates. Predictors of health outcomes will be analyzed by ANCOVA or multiple regression as independent variables, with change in the WORC as the dependant variable. All statistical tests will be two-sided and statistical significance will be denoted by a computed *p* value equal to or less than 0.05. All data analysis will be carried out according to a pre-established analysis plan. The statistical analysis plan (SAP) will be carried through blinded according to group allocation, and results will be interpreted in an author consensus statement prior to disclosing/revealing group allocation on the basis of a blinded review of the data from the primary endpoint (changes from treatment A compared to changes from treatment B), assuming that treatment A is the active treatment (PR), and the other assuming that treatment B is the active treatment (UC). Analysis of the primary outcome will be calculated blinded, and two interpretations will be performed based on whether PR or UC is superior. Not until signed consent from all of the authors of this trial (identical to the authors of this SAP) has been obtained, agreeing on one interpretation of the results only, will the randomization code be broken. This is to reduce bias in the interpretation of the current findings. On agreement, all members of the author group will approve and sign the interpretations before any publication procedures are initiated [76].

The protocol conforms to the recommendations of the Enhancing the Quality and Transparency Of health Research (EQUATOR) network [77] using the Standard Protocol Items: Recommendations for Interventional Trials (SPIRIT) checklist and the Consolidating Standards of Reporting Trials (CONSORT) statement [78] (Additional file 3).

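### The secondary-outcome models omit age, a stratification factor, which is mildly conservative; and surgery information, fixed before randomisation, is listed as an outcome

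*Protocol article*

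**What the plan says.** **Randomisation.** Under Allocation, randomization and sequence generation, the article gives the purpose and the factors: "To counter potential imbalance in the randomization, stratification by trial site and age", with age cut at 57 years and permuted blocks of 4 to 8. Allocation follows baseline testing and surgery.

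**Primary model.** The section Statistical analysis plan has fixed factors for group, time, gender and site, "whereas age and baseline values will be analyzed as covariates". Age is therefore named separately from the baseline values.

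**Secondary models.** The next sentence assigns logistic regression to binary outcomes and "ANCOVA for the continuous outcome measures (pain, patient-reported outcomes, surgery information, strength, ROM) as dependent variables", "with group allocation and time as fixed factors, and site and baseline values as covariates". Neither age nor gender appears.

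**Surgery information.** Outcome measures/variables describes it as "intraoperative information (including details of tendon repair". Patients and settings gives the order of events: "After surgery the orthopedic surgeon provides surgery information", and randomisation comes next.

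**The concern.** There are two separate matters in one sentence of the plan.

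First, one stratification factor (site) is carried into the secondary models and the other (age) is dropped without a reason. Stratified blocking already balances age between the arms, so age contributes little to the variability of the treatment contrast. A model without age still counts the variance due to age as residual error. Its standard error then overstates the true uncertainty, and the precision gained by stratifying is not used. Strength, range of motion, pain and DASH would be affected to the extent that age predicts them. Primary and secondary results would also be adjusted differently with no explanation.

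Second, a between-group test of something settled before allocation cannot show an effect of rehabilitation. A chance difference in operative detail would sit among the secondary outcomes as if it could.

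**Working it through.** **Inputs from the article.** 100 patients, 50 per arm, 1:1; two named sites; age split at 57; blocks of 4 to 8; two-sided 5% tests; planning difference 12 points, SD 20.

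**Assumption.** R² is the share of outcome variance explained by age after adjustment for site and the baseline value. The article does not give it, so it is varied from 0 to 0.30. The article states no target difference for the secondary outcomes, so the planning difference for WORC (12/20 = 0.6 SD) serves as the yardstick.

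**Step 1: the article's own figure.** Standard error = 20 × √(2/50) = 4.0, and 12/4.0 = 3.0. Power = Φ(3.0 − 1.96) = Φ(1.04) = 85.1% (84.4% with the t distribution). The stated 85% is reproduced.

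**Step 2: formula for omitting the stratifier.** The model standard error is too large by 1/√(1 − R²), and the true two-sided size is 2 × [1 − Φ(1.96/√(1 − R²))].

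- R² = 0.05: ratio 1.026, size 4.4%
- R² = 0.10: ratio 1.054, size 3.9%
- R² = 0.20: ratio 1.118, size 2.8%
- R² = 0.30: ratio 1.195, size 1.9%

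**Step 3: simulation with the article's design.** Blocks of 4, 6 or 8 within site by age stratum; ANCOVA at a single time point on group, site and baseline value, fitted without and with age; no missing data; residual SD 20. There were 10,000 runs for size and 3,000 for power in each setting. With age acting through the stratum:

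| R² | Size, age omitted | Size, stratum included | Power, age omitted | Power, stratum included |
|---|---|---|---|---|
| 0 | 4.8% | 4.8% | 84.5% | 84.5% |
| 0.05 | 4.7% | 5.2% | 84.8% | 86.0% |
| 0.10 | 3.9% | 5.2% | 84.8% | 87.2% |
| 0.20 | 3.0% | 5.0% | 87.3% | 92.3% |
| 0.30 | 2.1% | 5.4% | 87.3% | 94.4% |

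Monte Carlo error on size is about √(0.05 × 0.95/10,000) = 0.2 points, so the row for 0.05 cannot be told apart from no distortion. The mechanism is visible at R² = 0.20: the mean model standard error is 4.02 against an empirical 3.61, a ratio of 1.11, close to the formula.

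**Step 4: age acting linearly.** The distortion of size is smaller, because the split at 57 captures only part of the age effect: 4.7%, 4.3%, 3.8% and 2.9% at R² = 0.05, 0.10, 0.20 and 0.30. The power forgone is of the same order as in Step 3. At R² = 0.10 it is 84.3% without age, 86.5% with the stratum and 87.8% with continuous age; at R² = 0.20 it is 85.6%, 88.8% and 91.1%.

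**Step 5: surgery information.** The order is baseline tests, operation, surgeon's report, randomisation. Under valid randomisation the null hypothesis is true by design, so every p ≤ 0.05 is a false positive: 5% per variable. For independent variables the chance of at least one is 1 − 0.95³ = 14% with three and 1 − 0.95⁵ = 23% with five. The specified model does not fit either: it has a time factor and a baseline covariate, whereas an operative detail is recorded once and has neither a baseline value nor follow-up values.

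**The case against.** A reader might infer that the secondary tests are invalid, or that they produce too many positive findings. The article does not support that. Omitting age can only make these ANCOVA tests conservative, and no treatment effect becomes wrongly significant because of it. Nor can one say outright that the intervals are needlessly wide: that requires age to be prognostic after adjustment for baseline and site, and no figure is given. At R² of about 0.05 or less the effect is negligible. This part of the objection stands in full.

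It is also right that the formula belongs to linear models. In logistic regression, adding a prognostic covariate generally raises the standard error of the log odds ratio and moves the estimate away from the null. These models were not simulated, so nothing numerical is claimed for re-tear, healing or complications.

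On surgery information, the fair reading is a drafting slip. The article elsewhere counts the tendons involved and any supplementary procedures among the demographic data intended for the predictor analysis, and the stated model could not sensibly be fitted to such variables. That makes the correction easy but does not remove the need for it, since the sentence names the item as a dependent variable.

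Two defences fail. Age cannot be read into the baseline values of the secondary models, because the primary model lists the two separately. The article does refer to a pre-established analysis plan, which is not at hand, but it states the secondary model terms itself, so this is not detail left to another document.

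**Conclusion.** Both textual points hold, and both are minor. For continuous secondary outcomes, dropping age is conservative: negligible at R² up to about 0.05; for an age-stratum effect, size about 3.9% with about 2 points of power lost at 0.10, and about 3% with about 5 points lost at 0.20. With a linear age effect the distortion of size is smaller. These figures rest on an assumed R², complete data, a single follow-up time and the WORC planning difference. Listing surgery information as an outcome is wrong whatever R² is, because allocation comes after it. The primary analysis is not touched: it includes both site and age.

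**What to change.** Add age to the secondary ANCOVA models, either as the stratification factor or in the form used in the primary model, and state which. This costs one degree of freedom per model. Add it to the logistic models where the number of events allows. The argument here is for age as a stratifier. Copying the whole primary covariate set would bring in gender as well and cost a further degree of freedom; that is a separate choice.

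Delete surgery information from the dependent variables. Report it descriptively with the baseline characteristics, or use it as a predictor, in line with the demographic data described under Outcome measures/variables.

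Both changes are a matter of wording, need no new data, and are best made before the randomisation code is broken.

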**Methods:**

The current study is a randomized, controlled, outcome-assessor blinded, multicenter, superiority trial with a two-group paralleled design. A total of 100 patients with surgically repaired traumatic rotator cuff tears will be recruited from up to three orthopedic departments in Denmark, and randomized to either a progressive early passive and active movement program or a limited early passive movement program (usual care). The primary outcome measure will be the change from pre-surgery to 12 weeks post-surgery in the Western Ontario Rotator Cuff Index questionnaire. Secondary outcomes include the Disabilities Arm, Shoulder and Hand questionnaire (DASH), range of motion, strength and tendon healing characteristics from ultrasound measurements at 12 months follow up.

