Thus, the US investigation at 12 months involves quantitative measures of the repaired and contralateral SST thickness and neovascularity (NV), in addition to the SAS measured as the acromiohumeral distance (AHD). Ultrasound images are captured with the patients seated in an upright position, feet flat on the floor, neutral trunk posture, and head facing forward. For the SST thickness measure the patient has the hand on the affected side on the ipsilateral posterior hip with the humerus in extension and the tendon is measured in a longitudinal [72] and a transverse view [67]. AHD is measured in the neutral position (arm resting at the side) and respectively with 45° and 60° of active shoulder elevation in the scapular plane [72, 73]. SST neovascularity assessed by power Doppler is measured with the shoulder internally rotated with the dorsal side of the hand placed on the sacrum, and the elbow flexed and directed laterally [74].

Registered demographic data include age, gender, tendon(s) involved, supplementary surgery performed, hand dominance, history of trauma, occupation/employment and preoperative sports/recreational activity level. Demographic data and baseline measures will be used in the analysis of predictors of health outcomes.The investigator or site personnel monitor each patient for adverse events (AEs) throughout the study. Tendon re-tear is assessed by US at 6 weeks postoperatively and any re-tear is recorded. The investigator assesses and records any AE (in response to a query, observed by site personnel or reported spontaneously by the patient) in detail, including the date of onset, description, severity, duration and outcome, relationship of the AE to study intervention and any action(s) taken. All AEs will be followed closely to make sure that the patient is safely handled including follow up on clinical issues, until a stable situation is reached.

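### The ANCOVA for continuous secondary outcomes drops age (a randomisation stratum) and gender, both of which the primary WORC model includes

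*Protocol article*

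**What the plan says.** All passages are in the protocol article.

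- **Primary model** (Statistical analysis plan): an ANCOVA on WORC change, "with group allocation (two levels) and time (week 6 and 12), gender and site as fixed factors". Adjustment for age and for the baseline score is by covariate.
- **Continuous secondary outcomes** (same section): pain, questionnaire scores, strength, ROM and surgical details each get their own ANCOVA, and the terms are set out "with group allocation and time as fixed factors, and site and baseline values as covariates". Neither age nor gender is listed.
- **Randomisation** (Allocation, randomization and sequence generation): "stratification by trial site and age", with age cut at 57 years. Gender is not a stratum.
- **Data available** (Outcome measures/variables): "Registered demographic data include age, gender, tendon(s) involved".
- **Sites**: Patients and settings names two hospitals and allows more. The abstract has patients "recruited from up to three orthopedic departments in Denmark".

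**The concern.** The article lists both models term by term, so the difference between them is stated and is not simply left to a fuller document. Three things change between the primary and the secondary model: age goes, gender goes, and site moves from the fixed factors to the covariates. No reason is given for any of them.

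The two omissions do different harm.

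- **Age** was used to balance the arms. Stratifying reduces the true variability of the treatment estimate, but an analysis that ignores the stratum leaves the age variance in the residual. The reported standard error is then larger than the true one.
- **Gender** was not used to balance the arms. Leaving it out gives a correct standard error, but a larger one than necessary.

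ROM and muscle strength are named secondary aims, and the sample size was set on WORC alone. Precision on these outcomes therefore has no planned reserve.

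**Working it through.** The plan gives no figure on this point, and no age, gender or site effects. Every effect size below is an assumption, shown over a range.

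**1. Age: a stratum left out of the model**

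Let the residual SD be 1 once baseline, site and age are in the model. Let *a* be the age effect in residual SDs per SD of age. Assume normally distributed age, half the patients on each side of 57, and balanced strata.

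- Residual variance that the age-free model reports: 1 + a².
- A median split captures 2/π = 0.637 of the variance of a normal variable, and stratification balances that share. The variance that actually drives the treatment estimate is 1 + (1 − 0.637)a² = 1 + 0.363a².
- Reported SE / true SE = √[(1 + a²)/(1 + 0.363a²)].
- Type I error = 2[1 − Φ(1.96 × ratio)].

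| a | Share of residual variance, a²/(1+a²) | SE ratio | Type I error |
|---|---|---|---|
| 0.2 | 4% | √(1.040/1.015) = 1.012 | 4.7% |
| 0.4 | 14% | √(1.160/1.058) = 1.047 | 4.0% |
| 0.6 | 26% | √(1.360/1.131) = 1.097 | 3.2% |

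Simulation agrees (N = 100, two sites, blocks of 4, 6 or 8 within site-by-age strata, one time point, 3,000 trials, age effect 0.6, no gender effect):

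| Model | Mean SE | Empirical SD | Type I error |
|---|---|---|---|
| Secondary, as written | 0.2346 | 0.2151 | 3.1% |
| Plus gender, site as factor | 0.2359 | 0.2166 | 3.2% |
| Plus age, site as factor | 0.2014 | 0.1995 | 4.8% |

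The Monte Carlo error on a 5% rate is √(0.05 × 0.95/3000) = 0.4 percentage points. A rerun with 8,000 trials per effect gave type I errors without age of 4.9%, 4.2% and 3.3% at a = 0.2, 0.4 and 0.6. A further simulation at an assumed 0.6 SD age effect gave SE 0.184 against 0.174 and 3.7%. Hence about 3 to 4% at that effect.

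**2. Gender: a non-stratum left out**

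Take the within-gender SD as 1. Assumed inputs: share of men p = 0.5 or 0.65; gender gap at follow-up g = 0.5, 1 or 1.5; baseline gap kg with k = 0.5 or 1; within-gender correlation of baseline with follow-up r = 0.3, 0.5 or 0.7.

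- VarY = p(1−p)g² + 1; VarB = p(1−p)(kg)² + 1; Cov = p(1−p)kg² + r.
- Residual variance with baseline only = VarY − Cov²/VarB.
- With gender added = 1 − r².

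Example, p = 0.5, g = 1, k = 0.5, r = 0.5: 1.25 − 0.625²/1.0625 = 0.882 against 0.75. The cut is 1 − 0.75/0.882 = 15%, worth 0.882/0.75 − 1 = 18% more patients.

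Over all inputs the cut is 1 to 29%. At g = 1 it is 3 to 16%, worth 3 to 19% more patients.

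Validity is intact. Simulating a gender effect of 0.6 residual SD per SD of the gender indicator (a gap of 0.6/0.49 = 1.2 SD) and no age effect, the model as written gave SE 0.2335 against an empirical 0.2356 and type I error 5.4%. With gender added and site as a factor the SE was 0.201.

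**3. Both together**

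With age and gender effects of 0.4 each and two sites, the mean SE is 0.2303 as written and 0.2017 with the primary term set, a ratio of 1.14. Power for a treatment effect of 0.6 residual SD is 73% and 84%. Adding gender but not age leaves type I error at 3.6%; adding age but not gender gives 4.7%.

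**4. Site**

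With two sites, numeric and categorical coding gave the same SE (0.2303). With three sites and the middle-coded one shifted by 0.5 SD, numeric coding raised the SE from 0.2308 to 0.2356, about 2%.

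**The case against.** **Baseline adjustment may already absorb most of this.** Each model includes the outcome's baseline value, which carries part of any age or gender difference. That stands, and it is why the lower ends of the ranges are negligible. For strength, baseline is measured in a shoulder with a complete supraspinatus tear, so it may be an incomplete stand-in.

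**Choice of covariates is a preference, and the assumed ranges are wide.** For gender this largely stands: its omission is inefficient but not invalid, and the argument is strongest for isometric strength and weaker for pain or questionnaires. For age it does not, because age was chosen as a stratum and the primary analysis adjusts for it.

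**Any error is conservative and confined to secondary outcomes.** This also stands. A reader might infer that the treatment effects would be biased or that false positives would increase; nothing here shows either.

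**Site.** A reader might infer from the move of site to the covariates that it will be entered as a single number and that the standard errors will be wrong for that reason. The protocol does not support this. It does not say how site is coded, and a covariate may simply mean a categorical adjustment term. Two sites are named, and with two the coding is immaterial. Harm needs a third site, a numeric code and an outlying middle-coded site. Even then the SE rises by only about 2% at a 0.5 SD shift; type I error near 2.5% needs a full 1 SD shift.

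**Conclusion.** The point holds as an unexplained and avoidable inconsistency between the primary and secondary models. It is minor.

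- **Age** is the more important omission. If it is prognostic after baseline adjustment, the secondary tests are conservative: about 3 to 4% type I error at an assumed 0.6 residual SD per SD of age, which is a strong effect (26% of residual variance), about 4% at 0.4, and close to 5% at 0.2.
- **Gender** costs precision only. Adding it would cut residual variance by 1 to 29% over the assumed inputs, and by 3 to 16% at a 1 SD gap.
- **Site** is a matter of wording unless a third department opens.

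If age and gender add little beyond baseline, the loss is trivial, and the documents give no data to settle that.

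**What to change.** In the Statistical analysis plan section, give the continuous secondary ANCOVA models the same adjustment terms as the primary model: gender and site as fixed, categorical factors, and age and baseline value as covariates. Adding gender alone is not enough, because it leaves the stratum out.

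Keep the change to the continuous outcomes. The logistic models for re-tear, healing, recurrence and complications may have too few events to carry extra terms, and the text should make clear that their term list is separate.

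The change should be made before the blinded analysis. It uses one model degree of freedom for age, one for gender and one more if a third site opens, so two to three with 100 patients planned. Age, gender and site are already recorded, so no new data are needed.
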